**Research design and methods:**

We have designed a double-blind, randomized, placebo controlled study with selenium and/or vitamin E versus placebo as the interventions for patients with type 2 diabetes and chronic kidney disease (CKD) stages 1–3. A 2 × 2 factorial design will allow a balanced representation of the heritage groups exposed to each intervention. The primary biochemical outcome is change in GPx activity, and clinical outcome measure is the actual, rate of—and/or percentage change in estimated glomerular filtration rate (eGFR) from baseline. Analysis will be with a marginal model for longitudinal data using Generalized Estimating Equations corrected for measures of baseline serum antioxidant enzyme activities (GPx, superoxide dismutase and catalase), micronutrient levels (vitamins E and C), measures of inflammation (interleukin 6, c-reactive protein and monocyte chemoattractant protein-1) and markers of oxidative damage (plasma 8-isoprostaglandin F2α and urinary 8-hydroxydeoxyguanosine).

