## Subjects

We plan to recruit a total of 200 adult patients with type 2 diabetes of white, Caucasian and non-Caucasian (African, Caribbean or Indo-Asian) heritage from general practices in South West London, UK. An equal number of eligible patients will be randomized to receive, either, active selenium (200 μg once daily) or its placebo and/or vitamin E (400 IU once daily) or its placebo in a 2 × 2 factorial design (Fig. 1). Treatment allocation will be according to a computer generated code for each group to which the patients and researchers will be blinded.

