### Clinical follow-up procedures

All patients will receive their usual care according to the latest National Institutes of Clinical Excellence recommendations, in primary and secondary care settings [23]. Treatment will aim to achieve targets for blood pressure of ≤130/80 mmHg, glycated haemoglobin of 59 mmol/mol (<7.5 %) and LDL-cholesterol of ≤2 mmol/L (<100 mg/dL). Routine clinical and biochemical measurements and outcome assessments will be performed at the baseline visit and 1, 3, 6, 12, 18 and 24 months after randomization. All of the patient’s data will be anonymized.

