### Statistical analysis

In this 2 × 2 factorial design, selenium and vitamin E are considered the two factors. The data will be analyzed with a linear mixed model for longitudinal data [24]. In the model, eGFR is the dependent variable and time is an independent variable; the model will also contain as independent variables a dummy variable for each of the two factors, a term for the two-way interaction between the two factors, and continuous covariates for various measures of oxidative stress and inflammation at baseline. The model allows for the correlation between repeated measures on the same individual, but assumes that there is independence from one subject to the next. The correlation within measurements on a given subject will be modeled using compound symmetry as well as an autoregressive correlation structure. Whichever structure gives the best fitting model to the data will be used.

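### The eGFR model names no baseline eGFR, no heritage term and no treatment-by-time term, although the outcome is change from baseline; the precision cost runs from small to large, depending on how baseline is used

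*Protocol article*

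**What the plan says.** The Statistical analysis section describes a linear mixed model in which "eGFR is the dependent variable and time is an independent variable". The treatment part is "a dummy variable for each of the two factors, a term for the two-way interaction between the two factors". The only baseline covariates named are "continuous covariates for various measures of oxidative stress and inflammation at baseline".

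The abstract describes the analysis as "corrected for measures of baseline serum antioxidant enzyme activities (GPx, superoxide dismutase and catalase" and goes on to vitamins E and C, three inflammatory measures and two markers of oxidative damage, ten in all. That list is attached to a generalized estimating equations model, but it too contains neither baseline eGFR nor heritage.

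Three other places bear on baseline:
- The abstract's clinical outcome is the actual, rate of and/or "percentage change in estimated glomerular filtration rate (eGFR) from baseline".
- Under Clinical follow-up procedures, "outcome assessments will be performed at the baseline visit and 1, 3, 6, 12, 18 and 24 months after randomization".
- The Results section bases its effect sizes on change from baseline to 1 year and makes the selenium by vitamin E interaction the primary hypothesis.

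On heritage, the abstract says that the factorial design "will allow a balanced representation of the heritage groups exposed to each intervention", and the legend of Fig. 1 states the same aim. The Subjects section adds: "Treatment allocation will be according to a computer generated code for each group". The Results section compares eGFR slopes between heritage groups as a separate analysis.

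**The concern.** The outcome and the model do not match. The outcome is change in eGFR. The stated response is eGFR level, and no term lets the treatment effect develop over time. The factor dummies then estimate a difference in average level.

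- If only post-baseline visits are modelled, the between-patient spread in renal function stays in the treatment comparison. Under Subjects, the eGFR route admits values from above 45 to below 90, and the albuminuria route can admit higher values, so that spread is unlikely to be small.
- If the baseline visit is one of the response rows, the same dummies average over a visit at which no treatment has been given, which dilutes the effect.

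In neither case does the model use each patient's starting eGFR to sharpen the contrast, although it is measured in everyone. It is normally the best single predictor of later eGFR (general reasoning, not a statement in the article). The interaction pays most: with four equal cells its standard error is twice that of a main effect.

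Heritage is known at entry and is the factor that the design aims to balance, yet it is not a term in the treatment model.

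**Working it through.** **1. The plan's own power figures.** For an interaction contrast over four equal cells, SE = SD × √(16/N); power is from the noncentral t with N − 4 df, two-sided 5%.
- N = 150, effect 1.0 SD: 1.0/√(16/150) = 3.06, power 86.0% (stated 85%).
- N = 200, effect 0.85 SD: 0.85/√(16/200) = 3.01, power 84.9% (stated 83%).

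Both agree within 2 points. A main effect or a cell-versus-cell comparison would give about 99% or more, so the stated figures belong to the interaction, on the SD of 1-year change.

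**2. Assumption.** The article gives no within-patient correlation, so ρ is taken as 0.5 to 0.9. Variances below are in units of the single-visit variance. Percentage cuts apply equally to main effects and to the interaction.

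**3. Levels at the six post-baseline visits, baseline unused (compound symmetry).** Without baseline, V = ρ + (1 − ρ)/6. With baseline as a covariate, V = ρ + (1 − ρ)/6 − ρ². The last column uses the variance of mean change, V + 1 − 2ρ with V unadjusted, as comparator.

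| ρ | Unadjusted | Adjusted | Cut | Cut against mean change |
|---|---|---|---|---|
| 0.5 | 0.583 | 0.333 | 43% | 43% |
| 0.6 | 0.667 | 0.307 | 54% | 34% |
| 0.7 | 0.750 | 0.260 | 65% | 26% |
| 0.8 | 0.833 | 0.193 | 77% | 17% |
| 0.9 | 0.917 | 0.107 | 88% | 9% |

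With AR(1) by visit number (generalized least squares over the six visits) the cut in levels is 11, 20, 34, 53 and 77%. AR(1) in calendar time, with ρ as the 12-month correlation, gives 83-98%, so the AR(1) result depends on how ρ is defined.

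**4. Change from baseline to 12 months, the scale of the power statement.** Let ρ be the correlation of baseline with 12-month eGFR. The change score has variance 2(1 − ρ) and the baseline-adjusted analysis 1 − ρ², a saving of (1 − ρ)/2: 25, 20, 15, 10 and 5%. Power at N = 200 and 0.85 SD rises from 84.9% to 93.2, 91.7, 90.0, 88.3 and 86.6%.

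**5. Baseline visit as a response row, dummies as written (compound symmetry).** The effect shrinks to 6/7. The effect-scaled variance is [ρ + (1 − ρ)/7]/(6/7)²: 0.778 at ρ = 0.5 and 1.244 at ρ = 0.9. Against these, the adjusted variances in step 3 are 57% and 91% smaller.

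**6. In eGFR units.** Assume intercept SD 13, slope SD 3 per year and visit SD 5 (none in the article). The mean follow-up time is (1+3+6+12+18+24)/6 = 10.67 months = 0.889 year. For 100 v 100:
- Mean level: 169 + 9 × 0.889² + 25/6 = 180.3; SE = √(180.3 × 2/100) = 1.90.
- Mean change: 25 + 7.11 + 4.17 = 36.3; SE 0.85.
- Baseline-adjusted: 180.3 − 169²/194 = 33.1; SE 0.81.

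For an assumed benefit of 1.5 mL/min/1.73 m² per year (mean difference 1.5 × 0.889 = 1.33), power is about 11%, 35% and 37%.

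**7. Heritage.** For two equal groups differing by d SD, the share of variance explained is (d²/4)/(1 + d²/4): 1.0, 2.2 and 5.9% for assumed d of 0.2, 0.3 and 0.5.

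**The case against.** A reader might infer that most of the available precision is lost. The documents do not support that. It holds only if follow-up levels are analysed with baseline discarded, and the article nowhere says so. The outcome is defined as change, baseline is an outcome visit, and the power statement is on 1-year change. On that scale the example in step 6 improves only from an SE of 0.85 to 0.81. If baseline is a response row and treatment-by-time terms exist in the full plan, most of the baseline information is recovered without a separate covariate. The markers may also carry some of it: if they explain 30% of the eGFR variance, the 43% cut at ρ = 0.5 becomes 20%. All of this stands, and it limits the size of the finding.

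A reader might also infer that omitting heritage makes the standard errors wrong. That needs stratified allocation, which the article never states. The code for each group may refer to treatment arms, and the stated balance is an aim rather than a method. Any such error would be conservative, and heritage is examined separately through the slope comparison.

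The last objection is that an article condenses its plan, so covariate detail may lie elsewhere. That is fair for what is left unsaid. Here, however, the model's terms are set out and the named covariates pass over the baseline value of the response itself. The stated response also does not match the stated outcome. With randomisation the omission does not bias the treatment estimate; the issue is precision and a clear estimand.

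**Conclusion.** The point holds in a limited form. The stated model omits baseline eGFR, heritage and any treatment-by-time term, and it does not say how baseline enters although the outcome is change from baseline.

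The cost depends on what is actually done. It is 43-88% of the variance of the six-visit mean if levels are analysed without baseline (compound symmetry, ρ 0.5-0.9), and 11-77% with AR(1) by visit. It is about 5-25% if 12-month change scores are analysed and baseline and 12-month eGFR correlate at 0.5-0.9. All of these rest on assumed correlations. The heritage part is minor: about 1-6% of variance under assumed group differences, and a question of valid standard errors only if allocation was stratified. The change is worth making before analysis, but the article does not show that the trial has lost most of its precision.

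**What to change.** In the primary model, state one of two forms:
- post-baseline eGFR as the response, with baseline eGFR as a covariate; or
- all seven visits as the response, with a common baseline mean across the four arms and treatment-by-time terms for each factor and for their interaction.

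Name the contrast that tests the primary hypothesis, so that it matches the change-from-baseline outcome. Add heritage group (Caucasian / non-Caucasian) as a fixed effect, and say whether allocation was stratified by it. The biomarker covariates can move to a secondary model.

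The cost is wording in the analysis plan. Both variables are already collected, and no extra patients, visits or assays are needed.

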## Results

The primary hypothesis of interest in this study is whether there is an interaction between the selenium and Vitamin E supplements. If interaction is present, then the effect of each supplement will have to be estimated separately in the presence and absence of the other supplement. If no interaction is present, then it will be possible to estimate the main effects of selenium and Vitamin E separately without having to take the other supplement into consideration.

The effect sizes are conservative and will be based on the estimated changes from baseline to 1 year [25]. A study population of 150 will have 85 % power to detect an ES of 1.0 SD, and a population of 200 will have 83 % power to detect an ES of 0.85 SD at a two-sided alpha level of 5 % [26].

The two heritage groups will have their eGFR slopes compared over time and considered as either, (a) Caucasian and non-Caucasian, or (b) High and Low levels of oxidative stress/inflammation, with the oxidative stress and inflammation markers dichotomized at their median value. The power will not be heavily dependent on any of the assumptions; regardless of the true value of the underlying correlation among observations with subjects, of the correlation structure, of the attrition rate, or of the number of repeated measurements.

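### The Abstract plans GEE and the Methods a mixed model with a correlation structure picked by fit; if eGFR slopes vary between patients, that model misstates the error of slope comparisons

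*Protocol article*

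**What the plan says.** The protocol article describes the longitudinal analysis twice.

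- Abstract, Research design and methods: "Analysis will be with a marginal model for longitudinal data using Generalized Estimating Equations".
- Statistical analysis: "The data will be analyzed with a linear mixed model for longitudinal data". On the covariance it adds "The correlation within measurements on a given subject will be modeled using compound symmetry as well as an autoregressive correlation structure", and then "Whichever structure gives the best fitting model to the data will be used". It names no fit criterion, random slope or robust standard error.

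The fixed effects in the Statistical analysis section are time, "a dummy variable for each of the two factors, a term for the two-way interaction between the two factors", and baseline covariates. No term crosses a supplement or a heritage group with time.

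Slopes are nevertheless a target. The Abstract says the "clinical outcome measure is the actual, rate of—and/or percentage change in estimated glomerular filtration rate (eGFR) from baseline", and the Results section says "The two heritage groups will have their eGFR slopes compared over time". Under Clinical follow-up procedures, assessments are "performed at the baseline visit and 1, 3, 6, 12, 18 and 24 months after randomization", which is seven unequally spaced measurements.

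**The concern.** GEE and a likelihood mixed model are different estimators. GEE normally reports sandwich standard errors, which tolerate a wrong working correlation, but unweighted it needs data missing completely at random. A likelihood mixed model tolerates data missing at random, but its usual standard errors depend on the covariance model. Over 24 months some attrition is likely, so the choice can matter.

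The mixed-model version raises a second problem. Between-patient variation in slope is part of the error of any slope comparison. Compound symmetry leaves it out, because it implies that patients in a group share one true slope. An autoregressive structure lets correlation decay with separation, which is a different pattern from stable patient-specific slopes. Choosing the better of the two by fit does not make either right. At stake are the p-values and intervals for the heritage slope comparison, and for supplement effects on rate of decline if these are estimated from the same model.

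**Working it through.** **The plan's own figures.** The documents give no eGFR SD, slope SD or correlation, so there is no stated figure on this point to reproduce. The power figures in Results concern something else. They roughly fit an interaction contrast on a single change score with SE = 4·SD/√N: 86.5% at N = 150 (stated 85%) and 85.2% at N = 200 (stated 83%). They do not bear on slope standard errors.

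**Inputs for the slope check.** From the documents: visits at 0, 1, 3, 6, 12, 18 and 24 months. Assumed: intercept SD 10–12, residual SD σ = 4–6 and slope SD τ = 0–4 mL/min/1.73 m² (per year for τ), complete data, large-sample approximation.

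**Spread of visit times, in years.** Mean 64/12/7 = 0.762. Sum of squares 7.569. Sxx = 7.569 − 7 × 0.762² = 3.506.

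**Slope contrast under compound symmetry.** Per patient:

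- true slope variance = τ² + σ²/Sxx
- fitted within-patient variance = σ² + τ²·Sxx/6, so the model reports σ²/Sxx + τ²/6

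Group sizes cancel in the ratio R = reported/true. Type I error = 2[1 − Φ(1.96·√R)].

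At τ = 3, σ = 5: σ²/Sxx = 25/3.506 = 7.13. Reported 7.13 + 9/6 = 8.63; true 7.13 + 9 = 16.13. √R = √(8.63/16.13) = 0.731, and the error is 2[1 − Φ(1.434)] = 15.2%.

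| Slope SD τ | σ = 6 | σ = 4 |
|---|---|---|
| 0 | 5.0% | 5.0% |
| 1 | 5.9% | 7.1% |
| 2 | 8.6% | 12.6% |
| 3 | 12.6% | 19.0% |
| 4 | 16.9% | 24.5% |

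**Slope contrast under AR(1).** There is no simple formula. The best-fitting AR(1) was found by minimising expected deviance, and its reported standard error was compared with the true one. At τ = 3, σ = 6, intercept SD 12, AR(1) by visit number reports a standard error 1.595 times too large (error 0.2%). Across the assumed range the error is 0–2%. Continuous-time AR(1) is also conservative (0–0.9% over a wider range, σ 4–8 and τ 0–5).

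**Which structure would be chosen.** At τ = 3, σ = 6 the expected deviance per patient is 36.30 for compound symmetry and 37.44 for AR(1) by visit, so compound symmetry wins. AR(1) by visit fitted better only at σ = 4 with τ = 4–5.

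**Supplement interaction as literally written (no time interaction).** This contrast compares patient means over the visits. Compound symmetry reproduces the variance of a patient mean, so its standard error ratio is 1.00 and the error 5.0% at every τ. AR(1) by visit reports too small a standard error. At σ = 6, intercept SD 12 the ratio is 0.841 at τ = 0 (9.9%) and 0.871 at τ = 4 (8.8%); across the assumed range the error is about 7–11%.

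**Simulation check** (600 replicates per scenario, Monte Carlo error about 0.9 points, σ = 6). For the slope difference with model-based standard errors and the structure chosen by fit, type I error was 6.8%, 8.0%, 13.7% and 14.5% at τ = 0, 2, 3 and 4; compound symmetry was chosen every time. With sandwich standard errors it was 4.8–7.0% under working compound symmetry and 4.3–5.7% under working AR(1).

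**The case against.** The strongest reply has four parts.

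1. **A reader might infer that neither structure ever gives valid standard errors.** The documents do not support that. Compound symmetry is exact for slopes if true slopes do not vary, and no slope SD is given. GEE with sandwich errors, the usual form of the Abstract's method, largely removes the problem. This part stands. In the other direction, the Background and Discussion describe progression as differing with heritage, hypertension and proteinuria, so zero slope variation within a heritage group would be a surprising assumption.

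2. **A reader might infer that the supplement tests are inflated under compound symmetry and too cautious under AR(1).** For the interaction as written this is wrong on both counts: compound symmetry is valid and AR(1) is liberal. The slope figures apply to the heritage comparison, which is neither randomised nor the stated primary hypothesis. They reach the supplements only if a factor-by-time term is added.

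3. **A reader might infer that the autoregressive model treats unequal gaps as equal, or that the result is a lottery between the two structures.** The article does not say how the autoregressive lag is measured, and compound symmetry would usually be selected. The more likely outcome is too small a standard error for slopes.

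4. **An article may leave random effects and the standard-error method to a fuller document.** That is fair for omitted detail. It does not cover two conflicting methods, or a stated selection rule limited to two structures.

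**Conclusion.** The conflict between the Abstract and the Statistical analysis section is plain on the page and needs resolving; neither section labels its model as primary. The effect on slope comparisons is conditional: it requires that patients' true slopes differ and that model-based standard errors are used. Under the assumed residual SD of 4–6, it ranges from none at slope SD 0, through 9–13% type I error at SD 2, to 17–25% at SD 4 when compound symmetry is kept. AR(1) by visit errs the other way, at 0–2%. The supplement interaction as written is sound under compound symmetry and at about 7–11% under AR(1) by visit. The difference that dropout would make between GEE and the mixed model was not quantified.

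**What to change.** - Name one analysis, in the same words, in the Abstract and the Statistical analysis section. One suitable choice is a linear mixed model on actual time since randomization with a random intercept and slope; an unstructured covariance by visit, or robust standard errors, would also serve.
- Remove the rule that picks the correlation structure by fit.
- Add the group-by-time terms that the rate-of-change outcome and the heritage slope comparison need.
- Keep the other method, if wanted, only as a sensitivity analysis, and state the missing-data assumption of each.

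The cost is a change of wording before analysis. Intervals for slope contrasts will be slightly wider than under compound symmetry.

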## Results

The primary hypothesis of interest in this study is whether there is an interaction between the selenium and Vitamin E supplements. If interaction is present, then the effect of each supplement will have to be estimated separately in the presence and absence of the other supplement. If no interaction is present, then it will be possible to estimate the main effects of selenium and Vitamin E separately without having to take the other supplement into consideration.

The effect sizes are conservative and will be based on the estimated changes from baseline to 1 year [25]. A study population of 150 will have 85 % power to detect an ES of 1.0 SD, and a population of 200 will have 83 % power to detect an ES of 0.85 SD at a two-sided alpha level of 5 % [26].

The two heritage groups will have their eGFR slopes compared over time and considered as either, (a) Caucasian and non-Caucasian, or (b) High and Low levels of oxidative stress/inflammation, with the oxidative stress and inflammation markers dichotomized at their median value. The power will not be heavily dependent on any of the assumptions; regardless of the true value of the underlying correlation among observations with subjects, of the correlation structure, of the attrition rate, or of the number of repeated measurements.

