**Expected results:**

The study will assess the relationship between GPx activity, oxidative stress, inflammation and eGFR. It will test the null hypothesis that antioxidant therapy does not influence the activity of GPx or other antioxidant enzymes and/or alter the rate of change in eGFR in these patient groups.

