## Conclusions

In animal models of diabetes, there is overwhelming experimental evidence for a role of oxidative stress in renal pathophysiology. However, most clinical reports of antioxidant therapy have been post hoc analyses of surrogate markers, in non-specific populations with conflicting outcomes and safety concerns. We will primarily address renal functional decline in patients with diabetes at high risk of progressive disease. Importantly, it will investigate whether a nutraceutical approach to modulate an endogenous antioxidant pathway is safe and effective. The outcomes will help improve our understanding of the translation of oxidative metabolism in the development and treatment of renal disease.

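### The selenium by vitamin E interaction is named as the primary hypothesis and decides which treatment effects are estimated, which conflicts with the trial's stated aims

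*Protocol article*

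**What the plan says.** All references are to the protocol article.

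- **Results, primary hypothesis:** "The primary hypothesis of interest in this study is whether there is an interaction between the selenium and Vitamin E supplements".
- **Results, first branch:** "If interaction is present, then the effect of each supplement will have to be estimated separately in the presence and absence of the other supplement".
- **Results, second branch:** "If no interaction is present, then it will be possible to estimate the main effects of selenium and Vitamin E separately", with the other supplement then ignored.
- **Results, power:** 85% for 1.0 SD with 150 patients and 83% for 0.85 SD with 200, two-sided 5%. The contrast to which these effect sizes apply is not named.
- **Statistical analysis:** eGFR is modelled with a dummy variable for each supplement and a term for their interaction.
- **Abstract, Expected results:** "It will test the null hypothesis that antioxidant therapy does not influence the activity of GPx or other antioxidant enzymes". The same null hypothesis extends to how fast eGFR changes. No interaction is mentioned.
- **Abstract, Research design and methods:** "The primary biochemical outcome is change in GPx activity, and clinical outcome measure is the actual, rate of". The sentence ends by naming eGFR as the measure. The reason given for the design is heritage balance: "A 2 × 2 factorial design will allow a balanced representation of the heritage groups exposed to each intervention".
- **Abstract, Conclusions:** the aim is to explore whether the two supplements, singly or together, hold back a fall in eGFR.
- **Conclusions:** "We will primarily address renal functional decline in patients with diabetes at high risk of progressive disease".

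**The concern.** The document gives two different primary questions. One is whether the supplements act differently together than apart. The other is whether they change enzyme activity and slow renal decline. These are different hypotheses with different contrasts, and an answer to the first is not an answer to the second.

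The Results section also goes beyond putting an interaction term in the model, which is ordinary for a factorial trial. It uses the finding on that term to choose which treatment effects are estimated. The choice rests on the least precise contrast in the design, and one branch treats interaction as absent, which a non-significant result cannot establish. Two analysts could read the same document, name different primary results, and each cite the text.

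**Working it through.** **Inputs.** Total 200 patients, allocated equally in a 2 × 2 design (Subjects), read as 50 per arm. Two-sided 5%, with the power figures above (Results). Outcome in SD units, one summary value per patient, complete data (assumptions).

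**1. The plan's own power figures.** With four equal arms, the interaction (difference of differences) has SE = √(4/(N/4)) = 4/√N.

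- N = 150: SE = 0.327; 1.0/0.327 = 3.06; power = Φ(3.06 − 1.96) = 86.5% (86.0% with t on 146 df). Stated: 85%.
- N = 200: SE = 0.283; 0.85/0.283 = 3.01; power = Φ(3.01 − 1.96) = 85.2% (84.9% with t on 196 df). Stated: 83%.
- With an assumed 5% attrition, the normal formula gives 84.7% and 83.4%.

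A main effect (N/2 v N/2) would have over 99.9% power in both cases, and a two-arm comparison 99.1% and 98.9%. The stated figures therefore fit the interaction. They equally fit a two-arm comparison within one heritage half, since √(2/(N/8)) is also 4/√N, so the text does not settle which contrast was meant.

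**2. Precision of each contrast at N = 200.** The effect detectable with 80% power is (1.96 + 0.84) × SE.

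| Contrast | SE | Detectable effect | Power at 0.4 SD |
|---|---|---|---|
| Main effect, 100 v 100 | 2/√200 = 0.141 | 0.40 SD | 81% |
| Arm v arm, 50 v 50 | √(2/50) = 0.200 | 0.56 SD | 52% |
| Interaction | 4/√200 = 0.283 | 0.79 SD | 29% |

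The 95% CI for the interaction has half-width 1.96 × 0.283 = 0.55 SD, so even an estimate of exactly zero is compatible with interactions of about half an SD either way. The chance of missing a true interaction depends on its size, which the documents do not give below 0.85 SD:

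- 0.3 SD: 82% missed
- 0.4 SD: 71%
- 0.6 SD: 44%
- 0.85 SD: 15%

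For 80% power at 0.4 SD, about 785 patients are needed for the interaction and about 198 for a main effect.

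**3. What the primary hypothesis tests.** Let selenium alone add a, vitamin E alone add b, and the two together a + b. The interaction is (a + b) − a − b + 0 = 0, however large a and b are.

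**4. Error under the branch.** The rule was simulated as a 5% interaction test followed by 5% tests, with 50 per arm, 1,000,000 trials and no selenium effect. Chance of a false selenium claim:

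- main effect tested whatever the interaction: 5.0%
- branch, one arm-level comparison (without vitamin E) fixed in advance: 6.5%
- branch, two arm-level comparisons with Bonferroni correction: 6.9%
- branch, either arm-level comparison counts: 8.0%

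The interaction test itself rejects in 5.0%.

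**5. Power under the branch.** With an additive 0.4 SD effect, the main effect is both reached and significant in 0.95 × 0.807 = 76.7% of trials, against 80.8% in simulation when tested directly.

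**The case against.** The interaction may be a deliberate choice. The power figures fit it, the aims mention the supplements together, and each branch does estimate an effect for each supplement. The trial is not underpowered for its own assumption of 0.85 SD. The Results section speaks of estimating effects and sets no p-value rule, so the 6.5–8% is conditional on the branch being run as a test. All of this stands. It leaves untouched the conflict with the stated aims and the reading of a non-significant test as absence of interaction.

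Three stronger readings may tempt a reader, and none is supported.

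- **That the main effect is biased after a missed interaction.** Take selenium inert alone and 0.4 SD with vitamin E. The pooled estimate averages (0 + 0.4)/2 = 0.20 SD, which is the marginal effect itself. The main-effect weights (−½, ½, −½, ½) and interaction weights (1, −1, −1, 1) have zero cross-product, so conditioning on the interaction test does not move the estimate: it is 0.200 either way in simulation.
- **That the factorial advantage is lost.** The second branch still compares 100 with 100, and the power loss is about 4 points.
- **That dummy coding restricts each effect to half the trial.** The coding is not stated, and marginal contrasts can be taken from the same fitted model under any coding.

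**Conclusion.** The point holds as a contradiction in the primary hypothesis, together with a badly fixed rule for choosing effects. The Results section makes the interaction primary; the abstract and the Conclusions ask about effects on enzyme activity and eGFR. At 200 patients only an interaction of about 0.79 SD is detectable with 80% power, so the branch for no interaction cannot be entered on evidence of absence. The cost in error is modest: about 6.5–8% instead of 5% for follow-on claims about a supplement, with the primary interaction test unaffected. These sizes assume 50 complete patients per arm, equal variances, and the branch applied as a 5% test.

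**What to change.** 1. In Results, state as primary the marginal effect of selenium and the marginal effect of vitamin E (100 v 100 each) on the named outcomes: eGFR change as the clinical outcome and GPx change as the primary biochemical outcome. Estimate them whatever the interaction shows.
2. Delete the two conditional sentences. Always report the interaction with its 95% CI and the results of all four arms.
3. Name the contrast behind the 85% and 83%, and restate power for the main effects. On the assumptions above, 200 patients give 80% power at about 0.40 SD.
4. Align the abstract (Research design and methods, Expected results), Results and Conclusions.

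If the interaction really is the primary question, the abstract and aims must say so, and the main effects should still not depend on its result.

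The cost is rewording plus a restated power calculation; no design change is needed. The downside is that, with a true interaction, a marginal effect is an average over the other supplement. The arm results reported alongside make that visible.
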